### Collection and storage of blood

Blood collection will be performed after 12 h of fasting. Complete blood count, fasting glucose, glycated hemoglobin, serum lipids, liver enzymes, urea, creatinine, uric acid, thyroid hormones, fibrinogen, and C-reactive protein will be analyzed.

### Nutritional assessment

Nutritional assessment will consist of anthropometric and body composition evaluations. The anthropometric evaluation will include body mass, height, and Body Mass Index calculation, waist, hip, neck, and calf-girth measurements, as well as triceps, subscapular, and calf skinfolds. All measurements will be made in duplicate and the average values ​obtained will be used.

For the evaluation of body composition, a tetrapolar eight-point tactile electrode system will be used, which separately measures impedance of the subject’s trunk, arms, and legs at six different frequencies (1 kHz, 5 kHz, 50 kHz, 250 kHz, 500 kHz, 1000 kHz) for each of the body segments. The spectrum of electrical frequencies will be used to predict the intracellular water (ICW) and extracellular water (ECW) compartments of the total body water (TBW) in the various body segments (Inbody 720®, Bioespace Co. Ltd., Seoul, South Korea). The body composition analyzer has in-built hand and foot electrodes. Subjects will wear normal indoor clothing and be advised to stand barefoot in an upright position with their feet on the foot electrodes on the machine platform and their arms abducted with hands gripping on to the hand electrodes on the handles. Subjects are require to fast for the test [34].

### Nutritional counseling

Patients will receive individualized nutritional counseling according to the treatment guidelines for HF in order to achieve adequate weight. There will be monthly consultations with a nutritionist, in which specific nutritional guidelines for each patient will be considered, according to weight, age, and gender, with calculation of caloric and protein intake and food planning.

During consultations, patients will receive supplements in individual packs labeled with name, study identification code and dose number, containing 30 g of the supplement for 4 weeks of supplementation. Patients will be advised on how to prepare the supplement and on its ingestion schedule. Each patient is expected to return the empty packages at each visit as a form of control of the supplement consumption and will be instructed not to consume other nutritional supplements during the study.

### Food consumption

Twenty-four-hour food recall will be assessed in all consultations with nutritionists. Food records will be made for 3 days a month, on two working days (one common day and 1 day with Cardiac Rehabilitation program) and one weekend day. Patients will be advised not to perform the records on consecutive days. The Food Processor® program (ESHA, Salem, OR, USA) will be used to evaluate macro and micronutrient consumption.

### Quality of life

Quality of life will be assessed using the validated Brazilian version of the Minnesota Living with Heart Failure Questionnaire (MLHFQ) [35]. The questionnaire will be applied at times T0 and T12.

### Muscle strength

The evaluation of muscle strength will be performed monthly by means of the measurement of the handgrip force using the Jamar® brand hand-held dynamometer [36]. Participants will remain seated in a standard-height chair, with a neutral adducted and rotated shoulder, elbow flexed at 90 °, forearm in neutral position, wrist in dorsiflexion of 0–30 ° and ulnar deviation of 0–15 °. The dynamometer will be adjusted based on the participant’s hand size for optimum grip position. The test will be conducted with standard verbal instructions (such as, “one, two, three, tighten ... stronger ...”) and participants will be instructed to use the non-dominant hand first, followed by the dominant hand. Three measurements will be taken for each hand, with a 10–20 s rest interval between measures to avoid fatigue. The average value of the three measures will be used [37, 38].

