**Methods/design:**

This is a double-blind, randomized, placebo-controlled clinical trial in which patients with HF will be randomly allocated to two groups to receive supplementation with whey protein or placebo, associated with supervised exercise, for 12 weeks. The frequency of exercise will be three times a week. The study variables will be evaluated at baseline and 12 weeks. The main outcome will be maintenance of muscle mass and strength. Microvascular reactivity, quality of life, and inflammatory parameters will be evaluated as secondary outcomes.

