It is well established that food consumption is a strong stimulator of muscle protein synthesis [18, 19]. Intake of protein-rich meals in the form of free amino acids [20], milk protein [21], or meat [22] is able to stimulate muscle protein synthesis. This response depends on the amount, and also on the type of protein that is ingested [23]. Whey protein (WP) is a high-quality protein that has shown superiority in enhancing muscle protein synthesis compared with other protein sources in older adults, it is rapidly digested and has a high concentration of leucine [24] that plays an important role in the stimulation of postprandial muscle protein synthesis [25]. Leucine is one of the essential amino acids in the diet. It is capable, like all branched-chain amino acids, of avoiding hepatic alterations due to the lack of L-branched chain aminotransferase in the liver and its ingestion reportedly activates the mTOR pathway in skeletal muscle, contributing to a hypertrophy response [26].

Whey protein has already demonstrated a positive effect on protein synthesis and muscle mass gain [27] when associated with exercise [28, 29], but there are no studies in the academic literature that evaluate its benefits in patients with HF.

Currently, the most promising approach to treat depletion of nutritional status due to the disease appears to be a combination therapy that includes exercise, nutritional counseling, and drug therapy [4, 30], helping to manage symptoms, reducing the number of readmissions, and improving life quality [31].

Thus, the main objective of this study will be to evaluate whether supplementation with WP alone in association with 12-week supervised exercise will be able to preserve muscle mass in patients with New York Heart Association (NYHA) functional class I or II HF. As secondary objectives, an increase in muscle strength, an improvement in endothelial function assessed through microvascular reactivity, improvement in quality of life, and reduction of inflammatory markers will be evaluated.

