## Methods/design

### Study design and interventions

This is a double-blind, randomized, placebo-controlled clinical trial in which participants will be followed-up for a 12-week intervention period in which they will undergo supervised exercise through cardiac rehabilitation program participation. Participants will randomly be allocated into two groups to receive supplementation with WP alone or placebo and outcomes will be measured at baseline and upon completion of 12 weeks of study.

For the intervention group will be the supplementation of WP isolate at an amount of 30 g per day, totaling 27 g of protein and 120 kcal per serving. For the placebo group, maltodextrin will be given at an amount of 30 g per day, totaling 30 g of carbohydrates and 120 kcal per serving.

Patients will be instructed to consume supplements daily for 12 weeks, and consumption will be performed immediately after the training session on days of cardiac rehabilitation and on days without training, consumption will be performed at a time defined by the patient.

The study protocol complies with the Standard Protocol Items: Recommendations for Clinical Trials (SPIRIT) guidelines.

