### Endpoints

The main outcome will be maintenance of muscle mass and strength. Microvascular reactivity, quality of life, and inflammatory parameters will be evaluated as secondary outcomes.

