**Fig. 1 Fig1:**
[figure not shown]
Study flowchart

The procedures performed at the beginning of the study will be a cardiopulmonary exercise test (CPET), echocardiogram, microvascular reactivity test, blood collection for biochemical evaluation, handgrip-strength assessment, anthropometric and body composition evaluation, health-related quality of life assessment, and assessment of dietary intake. All initial evaluations will be repeated at 12 weeks.

All staff will be trained in the operation of the equipment for data collection and obtaining written informed consent. Additionally all members of the research team will participate in the work meetings to periodically evaluate the quality of the information collected, in order to minimize errors and ensure the reliability of the data. All the research team will be trained every 6 months during the research period.

Participants will receive a weekly structured telephone interview, with questions addressing side effects (mainly gastrointestinal), symptoms, adherence, and difficulties in carrying out the guidelines provided during the study.

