### Statistical analysis

Categorical variables will be presented as frequencies with percentages and will be compared using Fisher’s exact test and the chi-square test. Continuous variables will be presented as mean ± SD or median and interquartile range and will be compared using two-way analysis of variance (ANOVA) or Friedman’s test, whenever appropriate. A logistic regression analysis will be used to identify variables with an independent association with increase of lean muscle mass. A value of *p* < 0.05 will be considered statistically significant in all analyses. Calculations will be performed using the Statistical Package for the Social Sciences (SPSS 21.0 for Windows) program.

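### Handgrip strength, part of the main outcome, has two differing visit schedules and an ANOVA whose hypothesis depends on the visits entered; a baseline-adjusted week-12 comparison would settle it at no cost

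*Protocol article*

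**What the plan says.** **Timing.** The Muscle strength section says "The evaluation of muscle strength will be performed monthly by means of the measurement of the handgrip force" and gives no week numbers. The Abstract (Methods/design) says "The study variables will be evaluated at baseline and 12 weeks". Study design and interventions says "outcomes will be measured at baseline and upon completion of 12 weeks of study". Study procedures lists "handgrip-strength assessment, anthropometric and body composition evaluation" among the initial procedures and adds "All initial evaluations will be repeated at 12 weeks". None of these three places mentions interim handgrip readings.

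**Role of strength.** Endpoints: "The main outcome will be maintenance of muscle mass and strength". The Abstract says the same. The Background differs: "As secondary objectives, an increase in muscle strength, an improvement in endothelial function assessed through microvascular reactivity".

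**Test.** Under Statistical analysis, continuous variables "will be compared using two-way analysis of variance (ANOVA"), with Friedman's test as the alternative and significance at p < 0.05. The section does not name the factors, the visits entered or the term tested, and it mentions no baseline adjustment.

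**The concern.** The article fixes a test for continuous variables, but its two descriptions of the handgrip schedule turn that test into two different hypotheses. One asks whether the arms differ in change by week 12. The other asks whether the arms' profiles differ anywhere over the 12 weeks. Strength is named in the main outcome, so the conclusion could depend on a choice made after the data are seen. Neither version is the most efficient use of the baseline reading that is collected anyway.

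**Working it through.** **1. The plan's own figure.** Sample size gives 11 per group for a 500 g difference in muscle mass, SD 409.7 g, 95% confidence and 80% power. n = 2 × [409.7 × (1.960 + 0.842) / 500]² = 10.54, rounded up to 11. This reproduces. It concerns muscle mass; the article gives no effect, SD, correlation or time course for handgrip.

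**2. Assumptions for handgrip.** 11 per arm; two-sided 5%; visits at weeks 0, 4, 8 and 12 under the monthly schedule; equal correlation between visits (sphericity); group-by-time interaction as the tested term; and a week 0–12 effect that gives the two-visit test 80% power.

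**3. Two visits.** The interaction is F(1, 20), equivalent to comparing the change from week 0 to week 12. 80% power needs noncentrality λ₁ = 8.68.

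**4. Four visits.** The interaction is F(3, 60). Let p be the arm difference at each visit as a fraction of the stated effect, and S = Σ(p − p̄)². Then λ₃ = 2 × S × λ₁. With two visits and p = (0, 1), S = 0.5, which returns λ₁.

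| Time course of the arm difference | p at weeks 0, 4, 8, 12 | S | λ₃ | Power, 3-df test | Power, two-visit test |
|---|---|---|---|---|---|
| Linear | 0, 1/3, 2/3, 1 | 0.556 | 9.64 | 71% | 80% |
| Quadratic | 0, 1/9, 4/9, 1 | 0.605 | 10.50 | 75% | 80% |
| Only at week 12 | 0, 0, 0, 1 | 0.750 | 13.01 | 85% | 80% |
| Plateau from week 4 | 0, 1, 1, 1 | 0.750 | 13.01 | 85% | 80% |
| From week 8 | 0, 0, 1, 1 | 1.000 | 17.35 | 94% | 80% |
| At weeks 4 and 8, gone by week 12 | 0, 1, 1, 0 | 1.000 | 17.35 | 94% | 5% (error rate) |

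The last row shows the difference in hypothesis most clearly. The four-visit test is nearly always significant although the arms are equal at week 12.

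**5. Sensitivity.** Borrowing the standardised muscle-mass effect instead (500 / 409.7 = 1.22), the two-visit test has 77.7% power. The four-visit test has 68.5% (linear), 82.3% (late or plateau) and 92.3% (from week 8). A 1-df linear-trend contrast on the monthly values would have 84.3% under linear growth. The spread has the same shape.

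**6. Baseline adjustment.** The change score has variance proportional to 2(1 − ρ). The week-12 value adjusted for baseline has variance proportional to 1 − ρ². The noncentrality is therefore multiplied by 2(1 − ρ)/(1 − ρ²) = 2/(1 + ρ), tested at F(1, 19).

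| Baseline to week-12 correlation ρ | λ = 8.68 × 2/(1 + ρ) | Power |
|---|---|---|
| 0.5 | 11.57 | 90% |
| 0.7 | 10.21 | 86% |
| 0.8 | 9.64 | 84% |
| 0.9 | 9.13 | 82% |

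This needs only the readings at baseline and week 12.

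**The case against.** A reader might infer that handgrip is measured *only* at baseline and week 12 in the other sections. The documents do not say so. A monthly schedule contains both visits, and repeating the initial evaluations at 12 weeks is compatible with extra readings in between. The schedule figure is not available here. The general sections may simply be summaries that omit the interim readings, and a week 0–12 comparison is possible on either reading. This stands, and it reduces the schedule point on its own to a matter of wording.

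A reader might also infer that the four-visit test is *weaker*. It is not so in general. It loses power under steady divergence and gains under several other patterns, and the article gives no handgrip time course to decide between them.

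Third, the ANOVA sentence is generic. It does not say that the interaction is the tested term or that monthly values enter it, and such detail is often left to a full protocol or analysis plan. The missing detail alone is therefore not the point. The point is that the method the article does name can be replaced by a better-defined and more efficient one with data already planned.

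Finally, the stakes are limited. The Background makes strength secondary, and the sample size rests on muscle mass, for which no monthly schedule is given. This also stands, but Endpoints and the Abstract still place strength in the main outcome.

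**Conclusion.** The point holds as a free improvement. The handgrip schedule is described in two ways that need reconciling, and the named test answers a 1-df or a 3-df question according to the visits entered. Against 80% power for the two-visit test, the four-visit test has about 71% to 94%, so the direction is open. What is firm is that the hypotheses differ and can lead to opposite conclusions. A week-12 contrast adjusted for baseline removes that ambiguity and has about 82–90% power for correlations of 0.9 to 0.5. That gain would exist under either schedule.

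The power figures rest on 11 per arm, equal correlation between visits, assumed visit weeks, an assumed interaction test and an effect set to give 80% power. None of the handgrip inputs comes from the article. The muscle-mass sample size is unaffected.

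**What to change.** 1. State the handgrip visits once, with week numbers, and make the Abstract, Study design and interventions, Study procedures and Muscle strength sections agree.
2. For strength, replace the ANOVA or Friedman's test with the between-arm difference at week 12 adjusted for baseline handgrip. Either ANCOVA, or a mixed model for the post-baseline monthly values with baseline as covariate and arm-by-visit terms, would serve.
3. Declare the interim months supportive only.
4. Align the Background with Endpoints on whether strength is a main or a secondary outcome.

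The cost is wording and a standard procedure, with no extra visits or data. The article reports recruitment as under way, so the change should be recorded before unblinding.

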### Functional capacity

All patients will undergo a symptom-limited CPET, performed on a treadmill (Ergo PC Elite, Micromed, Brasilia, Brazil) with a ramp protocol. Heart rate and blood pressure will be measured every minute during exercise and recovery. A 12-lead electrocardiogram (ECG) will be continuously evaluated and will also be recorded every 3 min. After calibration of the volumes and gas exchange analyzers, patients will breathe through a mask connected to a two-way respiratory valve. Expired gases and volumes will be analyzed (VO_2000_, MedGraphics, St. Paul, MN, USA) [39].

### Echocardiogram

Conventional echocardiography will be performed in all patients using standard views, with the patient in the left lateral decubitus position, using a commercially available ultrasound machine (Vivid E9, GE Healthcare, Horten, Norway). Echocardiographic images will be obtained by a single experienced examiner and recorded for a second analysis by another experienced observer. Both will be blinded to patient allocation. Left ventricular ejection fraction (LVEF) will be calculated using the Simpson method, and all other parameters will be obtained and analyzed in accordance with the criteria defined on EAE/ASE/EACI guidelines [40, 41].

### Exercise training protocol

The exercise program will consist of supervised aerobic and strength exercises, three times a week for 12 weeks. Aerobic training will occur before strength training and will start with a 7-min warm-up at 40% of the maximal functional capacity (MFC) obtained from baseline CPET, ending with a cooling-down of 3 min at 30% of MFC (Table 1).

**Table 1 Tab1:** Exercise training, prescription, and monitoring of patients on the cardiac rehabilitation program

Type of exercise		Intensity of exercise	Duration of sessions	Monitoring	Weekly frequency
Continuous exercise	Aerobic training (walking)	60–70% VO_2_max	30 min	BS (levels 12–14), BP, ECG and HR	Once a week
High-intensity interval training	Aerobic training (walking)	8 sets of 40 s at 90–95% VO_2_max separated by 110 s of moderate-intensity exercise at 50% VO_2_max	Approximately 20 min	BS (levels 12–14), BP, ECG and HR	Twice a week
Strength training	Dynamic with machine weights (quadriceps, hip, trunk, dorsal and pectoral)	3 sets of 10 repetitions (30–40% of body weight)	Approximately 30 min	Symptom-limited exercise test with HR and BP will be monitored at 10-min intervals	3 times a week

*VO*_*2*_*max* maximal oxygen uptake, *HR* heart rate, *BP* blood pressure, *BS* Borg Scale, *ECG* electrocardiogram

Once a week, patients will undergo a continuous exercise training protocol consisting of 30 min at 60–70% of MFC. Training intensity will be controlled using a heart rate monitor and the Borg Scale score aiming at levels 12–14 during the training session, as recommended in the current exercise guidelines for HF patients [16]. Twice a week, a high-intensity interval training protocol will be performed, with eight sets of 40 s at 90–95% of MFC separated by 110 s of moderate-intensity exercise at 50% of MFC. Workload will be increased during the 12-week training period based on the Borg Scale of perceived effort. The Borg Scale score and heart rate will be determined after warm-up, at 20, 30, and 40 min of exercise, and after cooling down.

Strength training will be implemented three times a week after aerobic exercise sections and will consist of eight dynamic strength exercises for larger muscles (quadriceps (2), hip (2), trunk (2), dorsal (1), and pectoral (1)) with three sets of 10 repetitions at near-maximal load separated by 1-min rest intervals between sets. During strength training, heart rate, and blood pressure will be monitored at 10-min intervals, and the load will be increased progressively once the patients can successfully perform three sets of 10 repetitions. Participants will be instructed not to perform any other exercise during the study.

### Microvascular reactivity

A laser speckle contrast imaging system with a laser wavelength of 785 nm (PeriCam PSI system, Perimed, Järfälla, Sweden) coupled to iontophoresis of acetylcholine and sodium nitroprusside will measure non-invasively real-time cutaneous microvascular flow changes in the forearm [42]. For the post-occlusive reactive hyperemia (PORH) test, arterial occlusion will be performed with suprasystolic pressure (50 mmHg above the systolic arterial pressure) using a sphygmomanometer applied to the arm of the subject over 3 min. Peak skin flow will be measured after pressure release.

Images will be analyzed using the manufacturer’s software (PIMSoft, Perimed, Järfälla, Sweden). The measurements of skin blood flow will be divided by the mean arterial pressure to yield the cutaneous vascular conductance (CVC) in arbitrary perfusion units (APU)/mmHg, to avoid interference of blood pressure levels on calculation of microvascular flow.

### Statistical analysis

Categorical variables will be presented as frequencies with percentages and will be compared using Fisher’s exact test and the chi-square test. Continuous variables will be presented as mean ± SD or median and interquartile range and will be compared using two-way analysis of variance (ANOVA) or Friedman’s test, whenever appropriate. A logistic regression analysis will be used to identify variables with an independent association with increase of lean muscle mass. A value of *p* < 0.05 will be considered statistically significant in all analyses. Calculations will be performed using the Statistical Package for the Social Sciences (SPSS 21.0 for Windows) program.

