### Sample size

Considering a muscle mass gain of 500 g in the intervention group at 12 weeks compared to the placebo group, with a standard deviation (SD) of 409.7 g, 11 patients in each group are required to guarantee 95% confidence and 80% power to the study. The results obtained in a similar study with WP supplementation were used as a reference [33].

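### Friedman's test, the only rank method named for continuous outcomes, cannot compare two independent arms, so outcomes sent to it have no valid test of whey against placebo

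*Protocol article*

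**What the plan says.** The Study design and interventions section sets out a parallel trial: "Participants will randomly be allocated into two groups to receive supplementation with WP alone or placebo". On timing it adds that "outcomes will be measured at baseline and upon completion of 12 weeks of study". Under Endpoints, "The main outcome will be maintenance of muscle mass and strength". The Muscle strength section gives handgrip a denser schedule: "The evaluation of muscle strength will be performed monthly by means of the measurement of the handgrip force". All participants follow the same supervised exercise programme for the 12 weeks.

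The sample size targets a difference between arms in gain: "Considering a muscle mass gain of 500 g in the intervention group at 12 weeks compared to the placebo group". The spread assumed for it is 409.7 g, and the section concludes that "11 patients in each group are required to guarantee 95% confidence and 80% power to the study".

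The Statistical analysis section then says continuous variables will be "compared using two-way analysis of variance (ANOVA) or Friedman’s test, whenever appropriate". It names no other rank test for them. For the ANOVA it does not state the factors, the repeated-measures structure or the term that represents treatment.

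**The concern.** Friedman's test ranks values within each block and asks whether one condition ranks consistently higher than another. In this trial the repeated unit is the patient and the conditions are visits. A patient receives whey or placebo, never both, so treatment is constant within every block and cancels out of the ranks. The test can say that patients changed over time. It cannot say that one arm changed more than the other.

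It is also the only rank method on offer for continuous outcomes. An outcome judged unsuitable for ANOVA, which could well happen with C-reactive protein, the quality-of-life score or skin vascular conductance, would be left without a test of the randomised comparison. Exercise is expected to move many of these outcomes in both arms, so a significant Friedman result could be taken for an effect of the supplement when it is only the shared training effect.

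**Working it through.** **Inputs.** From Sample size: difference in gain 500 g, SD 409.7 g, 11 per group, 95% confidence, 80% power. Assumptions: two-sided 5% level; 409.7 g is the SD of change (the article does not say, but the effect is a gain); normally distributed changes, used only to attach numbers to the illustration.

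**1. The plan's own figure.** n per group = 2 × (1.960 + 0.842)² × 409.7² / 500² = 10.54, rounded up to 11. This reproduces the stated 11, as a comparison of two independent means. At 11 per group, power is 81.7% by the normal approximation and 77.7% by the two-sample t-test. The trial was therefore sized on a between-arm contrast.

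**2. Friedman's test with two visits.** If k of N patients increase, the statistic is (2k - N)² / N on 1 degree of freedom, with critical value 3.84. Group membership does not appear. Pooled over N = 22 it is significant when k is at least 16 or at most 6. Within one arm of 11 it is significant when k is at least 9 or at most 2.

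- *No whey effect, both arms gain 500 g.* The chance that a patient increases is Φ(500/409.7) = Φ(1.220) = 0.889. The binomial probability of significance is 0.99 pooled and 0.89 within the whey arm. Simulation (4,000 trials per scenario) gave about 99% and 89%.
- *True 500 g difference, as +250 g against -250 g.* The chances of an increase are Φ(0.610) = 0.729 and 0.271. The expected count of increases is 11 × 0.729 + 11 × 0.271 = 11, exactly half of 22. The probability of significance is 0.03; simulation gave about 3%.
- *True 500 g difference, as +500 g against 0 g.* Simulation gave about 47%.

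The same 500 g treatment effect thus gives 3% or 47%, and no treatment effect can give 99%. The test follows the average change over both arms, not the difference between them.

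**3. Monthly handgrip.** More visits give Friedman's test more conditions to rank within a patient, but the conditions are still visits. It remains a test of time.

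**4. The parametric route.** With two visits, the group-by-time interaction of a repeated-measures two-way ANOVA is the same test as the two-sample t-test on change. Simulated type I error was about 5% and power about 77-78% at a 500 g difference, in line with the 77.7% in step 1. This is the contrast the sample size assumes.

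Other terms behave differently. Here r is the correlation between baseline and week 12, assumed because the article does not give it:

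| Term read as the treatment effect | r = 0.7 | r = 0.9 | r = 0.99 |
|---|---|---|---|
| Group-by-time, repeated measures | 78% | 78% | 77% |
| Group main effect | 22% | 9% | 6% |
| Group-by-time, pairing ignored | 24% | 0.6% | 0% |
| Baseline-adjusted ANCOVA | 82% | 78% | 75% |

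(Simulated power, 11 per arm, +500 g against 0 g.)

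For ANCOVA the residual SD is 409.7 × √((1 + r)/2). By the normal approximation, power at 11 per arm is 91.1% at r = 0.5, 87.4% at 0.7, 83.6% at 0.9 and 81.8% at 0.99, against 81.7% for the change comparison. If the between-person SD of muscle mass is 2-5 kg (assumed), then r = 1 - 409.7²/(2 × SD²), which is 0.979 at 2,000 g and 0.997 at 5,000 g. In that range ANCOVA adds almost no power.

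**The case against.** Friedman's test is only the fallback, for use where appropriate. Nothing shows that muscle mass, the outcome behind the sample size, would take that route. Handgrip is measured monthly, and a within-patient test over several visits is a legitimate description there. A journal article may also leave model details to a fuller protocol or analysis plan that is not shown.

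Much of this stands. It limits the reach of the point to outcomes sent down the rank route, and the article cannot be faulted for leaving out ANOVA factors and terms. But the article did choose to name its tests, and one of them cannot answer the randomised question. That is an error in the text, not a gap for another document to fill. A legitimate within-patient use for handgrip does not supply the missing between-arm test.

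One could also note that randomisation is in blocks of two, so that successive whey-placebo pairs could serve as Friedman blocks. The Statistical analysis section gives no hint of this.

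**Conclusion.** The point holds for the rank route. As written, any continuous outcome analysed by Friedman's test has no valid comparison of whey with placebo, and a significant result would reflect change shared by both arms. That allocation drops out follows from the design and needs no numerical assumption. The 99%, 47% and 3% figures rest on 11 per arm, normal changes and 409.7 g as the SD of change.

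Three stronger readings are tempting, and the documents do not support them:

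- *A reader might infer that the two-way ANOVA also fails to estimate the treatment effect.* It does not fail if the repeated-measures group-by-time interaction is read, which is unbiased for the sized contrast. The low powers in the table belong to the group main effect or to ignoring pairing, and the article states neither. Offering a related-samples test as the rank counterpart suggests that repeated measures were intended.
- *A reader might infer that ANCOVA is required.* It is a sound choice that handles chance baseline imbalance, but leaving it out is a matter of efficiency, not validity.
- *A reader might infer that the trial will conclude from significance in the whey arm and its absence in the placebo arm.* No section states separate per-arm testing or such a rule.

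The sample size of 11 per group is unaffected by this point.

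**What to change.** In the Statistical analysis section:

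1. For the arm comparison, replace Friedman's test with a between-arm rank method: Mann-Whitney on change from baseline, or rank ANCOVA. If Friedman's test is kept for handgrip over time, label it as a within-patient description.
2. State that within-arm tests support no conclusion about treatment.
3. For the parametric route, name the treatment contrast as the group-by-time interaction of a repeated-measures ANOVA. Baseline-adjusted ANCOVA is an acceptable alternative. Report the between-arm difference with its 95% confidence interval.

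The cost is a few sentences. Baseline and 12-week values are already collected, ANCOVA would use one degree of freedom, and no extra patients or visits are needed. The article reports that recruitment is still under way, so the wording can be settled before the final analysis.
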